### Interventions

The interventions take place in the ED waiting room post-triage assessment and prior to consultation with a physician. Post-intervention, all participants will receive standard medical care from healthcare providers. The study hospital has an information sheet about AGE; however, education about AGE including whether the information sheet is given to parents/patients is at the discretion of the attending physician.

For this study, the experimental intervention is a 3-min, whiteboard animation video about a family’s experience with pediatric AGE (URL: https://www.youtube.com/watch?v=5N3gMtvkCqk&list=PLxWz0fEGuv6o5LrEpvdsmQFs5zB1dIFR8&t=17s&index=12). The sham control condition is a 3-min standard video developed by the Centres for Disease Control and Prevention about hand washing for infection control (URL: https://www.cdc.gov/cdctv/healthyliving/hygiene/fight-germs-wash-hands.html) [30]*.* Parents will view either the experimental or sham control intervention once on an iPad in the ED waiting room post-triage assessment. Disposable headphones will be provided with the iPads to maintain blinding. At the end of data collection in the ED (post-intervention questionnaire 1), parents can opt to receive a link to their assigned video via email to view as often as they wish from their own device(s). Parents from the experimental intervention group that are participating in the qualitative interview will view the whiteboard animation video again at the start of the interview.

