The following data will be collected over the course of this study:Pre-intervention questionnaire (baseline, see Additional file 1): Participants will complete a pre-intervention questionnaire that includes demographics, knowledge questionnaire, and Decision Regret Scale within the iCare Adventure platform on the iPad.**Participants will then be randomized to view the study intervention or the standard care intervention within the iCare Adventure platform on the iPad. This process will be seamless for the participants.Post-intervention questionnaire 1 (immediate, see Additional file 2): After viewing the intervention, participants will complete the knowledge questionnaire and Decision Regret Scale a second time. In addition, participants will complete two items assessing their own performance on the knowledge questionnaire and Decision Regret Scale and one item regarding the perceived value and benefit of the KT tool. They will also be asked if they would like a video link emailed to them. At the end of this questionnaire, parents will be informed that the post-intervention questionnaire 2 will be emailed to them 4 days after this ED visit for completion at their earliest convenience. Experimental intervention group parents will be asked about participation in a qualitative focus group at this time.Post-intervention questionnaire 2 (4–14 days post-ED, see Additional file 3): Participants will be emailed a secure link on day 4 post-ED discharge to complete the knowledge questionnaire and Decision Regret Scale a third time, two items assessing their own performance on the knowledge questionnaire and Decision Regret Scale, three items related to healthcare utilization, and three items related to the perceived value and benefit of the KT tool (if applicable). Reminders to complete post-intervention questionnaire 2 will be sent to those who have not completed the survey every third day (day 7, 10, 13) to complete the survey by day 14 post ED-discharge. Previous research has demonstrated that 82% of AGE cases are resolved in 3 days or less and 14 days [40] represents the outer limit for pediatric AGE resolution [41].Post-intervention semi-structured interview (sub-sample of experimental group, see Additional file 4): Participants in the experimental group indicating willingness to participate in an in-depth, semi-structured, qualitative interview will be contacted via telephone after completion of post-intervention questionnaire 2. Up to three phone calls will be made to establish interview date/time. Qualitative interviews will focus on satisfaction with iCare Adventure platform, perceived benefit and value of the KT intervention, and willingness to participate in future, similar research.

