
### Data analysis

All data will be aggregated and analyzed. Quantitative data will be downloaded from a secure Canadian server to SPSS for data cleaning and analysis [42]. Data cleaning measures may include recoding into categorical variables and comparing and recoding free-text responses where appropriate. Descriptive statistics and estimation are the recommended focus of pilot/feasibility trials [43, 44]. Descriptive statistics (e.g., frequencies and measures of variation and spread) will be calculated to describe the study groups. Analyses by outcome measure are presented in Table 3. Analyses will be conducted based on intention-to-treat.

Initial data will be collected to perform a sample size calculation for a full-scale trial [43]. Estimation for knowledge and decision regret outcomes will focus on calculating confidence intervals of different widths to illustrate strength of preliminary evidence [43, 44]. Confidence intervals for the difference of means (paired) will be presented for both potential effectiveness outcome measures to account for repeated measures [45]. The confidence interval for the difference of means from time 1 to time 2 for both groups will be calculated to examine initial change scores and the difference of means from time 2 to time 3 for both groups will be calculated to examine sustained change score. Confidence interval widths for both initial and sustained change measures will be set at 99, 95, 90, 85, 80, and 75% and presented together alongside a minimum clinically important difference (MCID) in a graph [46]. If each confidence interval crosses both 0 and the MCID, this is inconclusive evidence of effect; however, if each confidence interval both excludes 0 and crosses the MCID, there is evidence of a potentially clinically important difference. A confidence interval that is above or equal to the MCID indicates that at this level there is a clinically meaningful difference between the groups.

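### Sustained change is measured from just after the video (time 2) to follow-up (time 3), so a fully retained gain has a true value of 0 and cannot meet the plan's rule except by chance

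*Protocol article*

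**What the plan says.** The Data analysis section of the protocol article defines two change scores for knowledge and decision regret. The first is stated as: "The confidence interval for the difference of means from time 1 to time 2 for both groups will be calculated to examine initial change scores". The second follows: "the difference of means from time 2 to time 3 for both groups will be calculated to examine sustained change score".

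The Data collection section fixes the three times.
- Time 1 is before the video: "Participants will complete a pre-intervention questionnaire that includes demographics, knowledge questionnaire, and Decision Regret Scale".
- Time 2 is in the ED, straight after it: "After viewing the intervention, participants will complete the knowledge questionnaire and Decision Regret Scale a second time".
- Time 3 is at home: "Participants will be emailed a secure link on day 4 post-ED discharge to complete the knowledge questionnaire and Decision Regret Scale a third time", with reminders that aim at completion by day 14.

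Both change scores get confidence intervals at 99, 95, 90, 85, 80 and 75%, drawn beside the MCID, and one set of readings serves both. Intervals that contain both 0 and the MCID are inconclusive. Beyond that, "if each confidence interval both excludes 0 and crosses the MCID, there is evidence of a potentially clinically important difference". An interval at or above the MCID is read as clinically meaningful at that level. The section states no time 1 to time 3 contrast and gives no separate criterion for time 2 to time 3.

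The Interventions section places the video before the physician consultation. It adds that, in the care that follows for all participants, "education about AGE including whether the information sheet is given to parents/patients is at the discretion of the attending physician".

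**The concern.** A sustained effect is one that is still present later. The article's Background uses the word in that sense when it describes an earlier trial whose knowledge gain at 1 month was not sustained at 6 months. The planned contrast starts at time 2, after the gain has happened, so it measures what is added or lost from then on. The rule then asks this contrast to exclude 0 and reach the MCID, which is a test for a second gain.

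The time 2–3 interval also takes in the rest of the ED visit and any AGE education given in either arm. It is therefore a mixture of retention or decay and later care.

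Estimating potential effectiveness is a scientific objective in Table 1, and the pilot data are to feed the sample size of a full-scale trial. A durability measure that reads 0 when the benefit is completely kept would give the planners a misleading signal.

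**Working it through.** The protocol gives no sample size, SD or MCID value, so there is no figure to reproduce. The central result is algebra. The numbers after it only illustrate it.

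**1. Identity.** For any participant, (T3 − T1) = (T2 − T1) + (T3 − T2). If the gain is fully kept, T3 = T2 and the planned sustained change is 0 for any initial gain. This holds within an arm and for the difference between arms, whatever the SD, MCID or sample size.

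**2. Chance of qualifying under full retention.** The rule speaks of each confidence interval. With a true value of 0, the 99% interval lies wholly above 0 with probability 0.5%. All six must do so, so the chance is at most 0.5%; having to reach the MCID as well can only lower it. At the 95% level alone the ceiling is 2.5%.

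**3. Illustration for knowledge (0–8, higher is better). All inputs are assumed.**
- SD 1.5 and reliability 0.7, the latter also taken as the correlation between any two times.
- MCID = standard error of measurement = 1.5 × √(1 − 0.7) = 0.82.
- SD of change = 1.5 × √(2 × 0.3) = 1.16, for every pair of times.
- Experimental means 4 → 6 → 6 (full retention) or 4 → 6 → 5 (half forgotten). Sham means 4 → 4.2 → 4.2.
- 50 per arm with time 3 data. Between-arm SE = 1.162 × √(2/50) = 0.232. Interval = estimate ± z × SE.

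Between-arm differences in change:

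| Level (z) | Full retention, T2–T3: 0 | Full retention, T1–T3: 1.8 | Half forgotten, T2–T3: −1.0 | Half forgotten, T1–T3: 0.8 |
|---|---|---|---|---|
| 99% (2.576) | −0.60 to 0.60 | 1.20 to 2.40 | −1.60 to −0.40 | 0.20 to 1.40 |
| 95% (1.960) | −0.46 to 0.46 | 1.34 to 2.26 | −1.46 to −0.54 | 0.34 to 1.26 |
| 90% (1.645) | −0.38 to 0.38 | 1.42 to 2.18 | −1.38 to −0.62 | 0.42 to 1.18 |
| 85% (1.440) | −0.33 to 0.33 | 1.47 to 2.13 | −1.33 to −0.67 | 0.47 to 1.13 |
| 80% (1.282) | −0.30 to 0.30 | 1.50 to 2.10 | −1.30 to −0.70 | 0.50 to 1.10 |
| 75% (1.150) | −0.27 to 0.27 | 1.53 to 2.07 | −1.27 to −0.73 | 0.53 to 1.07 |

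Under full retention, time 1–3 lies above the MCID of 0.82 at every level, while time 2–3 crosses 0 without reaching the MCID, a case the rule does not name. With half forgotten, time 1–3 excludes 0 and crosses the MCID at every level, while time 2–3 is wholly below 0.

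**4. Range.**
- *Sample size.* At 20 per arm the 99% intervals are −0.95 to 0.95 (full retention, T2–T3), −1.95 to −0.05 (half forgotten, T2–T3) and −0.15 to 1.75 (half forgotten, T1–T3). At 150 per arm they are −0.35 to 0.35, −1.35 to −0.65 and 0.45 to 1.15.
- *Spread.* SD 1.0 to 2.0 with reliability 0.6 to 0.8 puts the MCID at 0.45 to 1.26. At the noisiest corner (SD 2.0, reliability 0.6) the upper 99% limit for half forgotten, T2–T3, is −0.08 at 50 per arm and +0.46 at 20 per arm. The size of the pilot therefore decides whether the interval excludes 0; the sign of the true value does not change.

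**5. What does qualify.** Take no initial effect and a 2-point gain after time 2 in the experimental arm only, at 50 per arm. The 95% interval for T2–T3 is then 1.54 to 2.46, above the MCID. The contrast rewards a late gain.

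**6. Why the time 1–3 interval cannot be recovered.** Var(T3 − T1) = Var(T2 − T1) + Var(T3 − T2) + 2 Cov, and the covariance does not follow from the two separate intervals. In the illustration each variance is 1.35 and the covariance is −0.675, so the total is 1.35. Treating the two changes as independent would give 2.70, and intervals too wide by a factor of √2.

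**The case against.** The best defence is the planned graph. Initial and sustained change are shown together, so a reader sees the time 1–2 gain beside the time 2–3 change, and the two point estimates add up in parents who have all three scores. Read as a pair, they separate a gain that was kept from one that never occurred. Time 2–3 is also a legitimate measure of decay, and for regret the change after the consultation is of interest in itself. The study is a pilot that tests no hypothesis. All of this stands. It does not rescue the rule, which reads each interval on its own, and the interval that would answer the question is neither planned nor derivable. An analysis plan that is not shown might add a time 1–3 contrast, but the article itself fixes what sustained change means and how it is read.

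Some stronger readings are tempting and are not supported.
- *Forgetting would be reported as harm.* The rule has no category for a negative interval. A modest loss need not exclude 0 at every level either: a single-arm loss of 0.5 with assumed SD of change 1.5 and 45 responders gives −0.95 to −0.05 at 95% but −1.10 to 0.10 at 99%.
- *The definition breaks the intention-to-treat statement.* The plan says "Analyses will be conducted based on intention-to-treat". Missing time 3 scores affect time 1–3 just as they affect time 2–3, so this is a separate missing-data question.
- *The rule favours the sham arm.* Later education is open to both arms. If sham parents caught up, time 1–3 would shrink too.
- *The pilot would choose the wrong primary time point.* Nothing in the article ties this rule to that choice.

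**Conclusion.** The point holds as a fault in what is written. The contrast called sustained change measures retention or decay, together with the effect of later ED care and education in both arms, and the 0/MCID rule is unsuited to it. That conclusion is exact and needs no assumption: full retention has a true value of 0, and all six intervals can then favour the video with a probability of at most 0.5%. Only a further gain after time 2 can meet the rule other than by chance.

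For decision regret, where lower is better, full retention also gives 0. The argument about forgetting applies to knowledge only.

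The interval limits above rest on assumed SDs, reliabilities, means and numbers per arm, and show direction and rough scale only. The consequence is a misleading durability signal and a missing effect estimate for the full-scale trial, not a wrong confirmatory conclusion.

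**What to change.** In the Data analysis section, define the sustained effect for knowledge and decision regret as the change from time 1 to time 3, compared between arms; for example, the between-arm difference at time 3 adjusted for the time 1 score. Apply the six-level interval display and the MCID rule to that contrast, with the favourable direction stated for each scale. Keep time 2 to time 3 under the name retention or decay, reported descriptively for each arm and without the 0/MCID rule. Note beside it that this interval includes the remainder of the ED visit.

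All three measurements are already collected, so the cost is a change of analysis wording, best made before the data are analysed.

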### Data storage and security

All data will be stored on secure Canadian servers that are compliant with data privacy and security regulations to safeguard medical information as per the Health Insurance Portability and Accountability Act of 1996 [54]. The server is protected by a firewall and is backed up daily. All data stored in the server database is anonymous. Once data collection is complete, all data will be transferred to the researchers for analysis and long-term, secure storage and deleted from the iCare Adventure servers. The questionnaires have been made to be anonymous. Participants will not be identified by name or be identifiable by their responses.

Interview data will be transferred between the research team and the third party, transcription contractor via a secure, online portal or by courier. Transcripts will be de-identified. All data will be transferred to the researchers for analysis and long-term, secure storage and deleted by the third party contractor once transcription is complete. Master lists will be stored on a secure Canadian server only accessible to the research team.

## Discussion

Pediatric AGE is a common childhood illness representing a large burden on our healthcare system. Connecting parents and families to effective, evidence-based patient education is key to effective decision-making and therapeutic management of pediatric AGE. Digital KT tools offer a promising approach to communicate complex health information to parents and families. The evidence-based whiteboard animation video being evaluated in this pilot trial has been tailored to the needs of parents and families seeking care for pediatric AGE in EDs. This study will inform the design and conduct of a full-scale, effectiveness trial by gathering key data in four domains: (1) scientific, (2) process, (3) management, and (4) resource. These results will impact the emerging field of knowledge translation efforts targeting health consumers and advance the science on the best mode of patient education for acute childhood illnesses.

## Abbreviations

AGE: Pediatric acute gastroenteritis
ED: Emergency department
KT: Knowledge translation
RCT: Randomized controlled trial
